Centralised randomisation of subjects in the study will be performed using the Interactive Web Response System (IWRS). To get familiar with the IWRS, the investigators will be trained to work with the system and receive the IWRS User Guide. A username and password are used to access the system. They are sent to the authorised employee of the trial site at the beginning of the study.

As a result of the randomisation procedure, the volunteer will be assigned a randomisation number. Randomisation codes will be kept by authorised personnel of the CRO responsible for the organisation and implementation of randomisation in this study.

1. Blinding

This study will be conducted according to a double-blind design, so neither the study doctor nor study participants will be aware of the vaccine (Ad5- nCoV or placebo) administered to the subjects.

The appearance of Ad5-nCoV and placebo vials and their packaging will be identical. Labelling of the products will be performed to maintain the blinding (masking).

1. Emergency Unblinding

Unblinding during the study is only possible in the case of emergency, e.g. in the case of a serious and/or unexpected adverse event related to the use of the investigational vaccines as judged by the investigator, if the treatment of such adverse event is not possible without the information about the administered product.

Information about the product assigned to the volunteer will be available to the investigator via the IWRS, and the unblinding procedure will be described in the IWRS User Guide.

All cases of emergency unblinding during the study must be fully documented.

1. Efficacy and Safety Endpoints
2. Efficacy Endpoints
3. Primary Efficacy Endpoint

Seroconversion rate (proportion of subjects with at least four-times increase in antibody titers against the receptor-binding domain [RBD] of the SARS-CoV-2 S protein) on Day 28 after vaccination.

1. Secondary Efficacy Endpoints

- Geometric mean titer of serum antibodies against the RBD and SARS-CoV-2 S protein on Day 14, 28 and 6 months after vaccination.
- Seroconversion rate (proportion of subjects with at least four-times increase in antibody titers against the RBD and SARS-CoV-2 S protein) on Day 14, 28 (S protein only) and 6 months after vaccination.
- Geometric mean fold-rise in titers of serum antibodies against the RBD and SARS-CoV-2 S protein on Day 14, 28 and 6 months after vaccination.

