- Geometric mean titer of neutralising antibodies against SARS-CoV-2 on Day 14, 28 and 6 months after vaccination.
- Seroconversion rate (proportion of subjects with at least four-times increase in neutralising antibody titers against SARS-CoV-2) on Day 14, 28 and 6 months after vaccination.
- Geometric mean fold-rise in titers of neutralising antibodies against SARS-CoV-2 on Day 14, 28 and 6 months after vaccination.
- Geometric mean titer of neutralising antibodies against the Ad5 vector on Day 28 and 6 months after vaccination.
- Geometric mean fold-rise in titers of neutralising antibodies against the Ad5 vector on Day 28 and 6 months after vaccination.
- Cellular immune response (the number of IFNy-secreting T cells [ELISpot]; percentage of CD4+ and CD8+ T cells expressing IFNy, TNF and IL-2 [flow cytometry]) on Day 14, 28 and 6 months after vaccination.

1. Exploratory Efficacy Endpoints

- Frequency of confirmed COVID-19 cases during 6 months after vaccination (except for the cases occurred during the first 14 days after vaccination).

A confirmed COVID-19 case means the presence of clinical manifestations and a positive laboratory test result for SARS-CoV-2 RNA.

- Frequency of confirmed COVID-19 cases requiring hospitalisation (except for the cases occurred during the first 14 days after vaccination).
- Frequency of severe COVID-19 cases (except for the cases that occurred during the first 14 days after vaccination).
- Frequency of lethal COVID-19 cases (except for the cases that occurred during the first 14 days after vaccination).

1. Safety Endpoints

- Reactogenicity (frequency and nature of systemic and local immunisation reactions on the day of vaccination and within 7 days after vaccination).
- Frequency and nature of adverse events (Day 0–Day 28) and serious adverse events (Day 0–Day 28; Day 0–Month 6).
- Vital signs.
- Physical examination results.
- Electrocardiography.
- Biochemistry.
- Haematology.
- Coagulation test.
- Urinalysis.
- Serum immunoglobulin E concentration.

1. Selection and Withdrawal of Subjects
2. Selection of Subjects

A total of 500 subjects aged 18–85 years old will be randomised into the study.

Volunteers will be invited to participate in the trial specifically through advertising. All advertising materials for potential subjects will be initially provided to the ethics committee for approval.

1. Inclusion Criteria

Subjects must meet all of the following criteria to be eligible for participation in the study:

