^15^Assessment of local and systemic reactions to the vaccine administration by the study doctor within 7 days after vaccination, including in 20 minutes (± 5 minutes), 2 hours (± 10 minutes) and 5–8 hours after immunisation on Day 0. Reactogenicity assessment is performed during the registration of adverse events.

^16^The investigation of the cellular immune response will be performed in a separate cohort of at least 60 subjects randomised at trial sites in Moscow.

^17^During each visit/phone contact after the day of vaccination, the signs of acute respiratory infection are assessed. In the case of any signs and symptoms related to COVID-19 after immunisation, it is necessary to follow the procedures described in section 8.3.

^18^Visit 1–5: all concomitant treatments. Visit 5–6: only treatments related to SAEs.

^19^Visit 0–5: all AEs. Visit 5–6: only SAEs.

1. Details on Study Periods and Visits
2. Screening/Visit 0 (Day −10...−1)

Screening will be performed in an outpatient setting during not more than 10 days. If necessary, the screening procedures may be performed within several days or on Day −1 before randomisation. Nevertheless, the eligibility of the subject should be confirmed after the completion of all tests and procedures and after the assessment of all the examination results.

At screening before any protocol required procedures, the volunteers will be invited to participate in this clinical trial and provided with the Subject Information Sheet and Informed Consent Form for review and making a decision on the participation.

The details about the informed consent procedure are provided in section 11.2.

After signing the Informed Consent Form, an individual identification number will be assigned to the volunteer by the investigator. In the case of early withdrawal from the study, the individual identification number will be reserved for the subject and will not be assigned to another volunteer. After receiving a written informed consent and assigning the number, the study doctor will complete and provide the volunteer with an original insurance policy for the period of the study (section 11.4).

The volunteer will also receive an emergency contact card. This card specifies that the volunteer is participating in this clinical trial and contains information about an emergency contact person.

During the screening period, the following procedures will be performed to assess the subject’s eligibility^^[[3]](#footnote-3)^^:

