The analysis for serum antibodies against the receptor-binding domain (RBD) and S protein of SARS-CoV-2 will be performed on Day 0, Day 14, Day 28 and Month 6 after vaccination. The pre-existing antibody titer will be the titer detected before the investigational product administration (on Day 0). The analysis will be performed at the independent central laboratory using the EIA.

Neutralising antibodies against SARS-CoV-2 and cellular immune response endpoints (the number of IFNy-secreting T cells [ELISpot]; percentage of CD4+ and CD8+ T cells expressing IFNy, TNF and IL-2 [flow cytometry]) will be analysed on Day 0, Day 14, Day 28 and Month 6 after vaccination. The analysis will be performed at the independent central laboratory. The investigation of the cellular immune response will be performed in a separate cohort of at least 60 subjects randomised at trial sites in Moscow.

Neutralising antibodies against Ad5 will be analysed on Day 0, Day 28 and Month 6 after vaccination. The analysis will be performed at the independent central laboratory.

Additionally, blood samples will be collected from all study participants on Day 0 (3 samples), Day 14 (2 samples), Day 28 (3 samples) and Month 6 (3 samples) after vaccination for the exploratory analysis of secondary immune response endpoints (additional assessments of neutralising antibodies, etc.). The tests will be performed at the central laboratory, and the results will be analysed outside the framework of the clinical trial report.

The investigators will be provided with a separate laboratory manual containing detailed instructions on handling biological samples (collection, storage and transportation).

- 1. Registration of COVID-19 Cases

Registration of COVID-19 cases will be performed for 6 months after vaccination via observation and phone contacts with study participants.

In the case of signs and symptoms related to COVID-19, the volunteers should immediately contact the study doctor by phone.

A suspected COVID-19 case means the presence of the following clinical manifestations of acute respiratory infection and the lack of any other reasons explaining the subject’s condition regardless of epidemiological anamnesis:

- body temperature > 37.5 °C

and at least one the following:

- cough (dry or with scanty sputum)
- dyspnoea
- chest congestion
- sore throat
- nasal congestion or moderate rhinorrhoea
- impairment or loss of smell (hyposmia or anosmia)
- loss of taste (dysgeusia)
- conjunctivitis

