- fatigue
- muscle pain
- headache
- vomiting
- diarrhoea
- skin rash.

If COVID-19 is suspected, the volunteer will have a SARS-CoV-2 RNA test at home (throat swab) using the PCR to detect the SARS-CoV-2 infection. In 3 days, the test will be repeated. Any positive result will be considered as a confirmed COVID-19 case.

If COVID-19 is confirmed, the volunteer will be required to report this to a local outpatient clinic or other medical institution, where he/she receives medical care. Further follow-up of the volunteer will be performed at the outpatient medical institution. After the recovery and required self-isolation period, the subject may resume visits to the trial site to undergo procedures scheduled according to the Protocol. To the first visit after the recovery, the volunteer should bring a discharge summary issued by the medical institution, where he/she has been receiving medical care due to the confirmed COVID-19 case.

The study doctor will record the information about the COVID-19 case on a separate form of the subject’s CRF including the following information:

- onset and end dates
- severity:
- mild
- moderate
- severe
- extremely severe
- need for hospitalisation (yes/no/unknown)
- fatality (yes/no/unknown).

To collect the information, additional phone calls may be made.

Analysis of confirmed COVID-19 cases is the exploratory efficacy endpoint and they should not be registered as adverse events.

- 1. Assessment of Safety
     1. Specification of Safety Parameters

The list of safety parameters is provided in section 5.3.2.

- - 1. Methods and Timing for Assessing, Recording, and Analysing Safety Parameters
       1. Reactogenicity Evaluation

The evaluation of reactogenicity is performed by the investigator during visits on the day of vaccination and within the following 7 days (Visit 1/Day 0 (in 20 minutes (± 5 minutes), 2 hours (± 10 minutes), and 5–8 hours after vaccination), Visit 2/Day 2, Visit 3/Day 7) as a part of the registration of adverse events.

Reactogenicity of the investigational product will be evaluated by the study doctor according to local (injection site) and general (systemic) reactions to the vaccine administration. These reactions are expected reactions to the investigational vaccine administration, and they should be assessed for all study subjects.

Local reactions include redness, swelling, tightness/infiltration, pain, itching, arm weakness.

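### Section 8.3 allows the study PCR swabs only when no other reason explains the illness, an undefined judgement that the COVID-19 endpoint does not contain, so cases may be missed

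*Protocol*

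**What the plan says.** Section 8.3 defines a suspected COVID-19 case as "the presence of the following clinical manifestations of acute respiratory infection and the lack of any other reasons explaining" the volunteer's condition. The manifestations are a temperature above 37.5 °C and at least one further listed symptom. Swabbing follows suspicion: "If COVID-19 is suspected, the volunteer will have a SARS-CoV-2 RNA test at home (throat swab) using the PCR", repeated after 3 days, and either positive result confirms the case. Table 14 and the subsection of 8.1 on SARS-CoV-2 RNA use the same trigger.

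Visits and phone contacts add no second route. Table 14, footnote 17, sends them back to the same place: "In the case of any signs and symptoms related to COVID-19 after immunisation, it is necessary to follow the procedures described in section 8.3". Between contacts, section 8.3 asks that "the volunteers should immediately contact the study doctor by phone" when symptoms appear.

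The endpoint in section 5.3.1, repeated in the synopsis and under the secondary objectives, reads: "A confirmed COVID-19 case means the presence of clinical manifestations and a positive laboratory test result for SARS-CoV-2 RNA". It says nothing about ruling out other causes. Cases in the first 14 days after vaccination do not count.

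**The concern.** The order of steps is the problem. The PCR is there to decide whether a febrile illness is COVID-19, yet section 8.3 asks for other explanations to be excluded before the PCR is done. It gives no criteria for an adequate other reason, no work-up to establish one and no review of the decision. Several listed symptoms, such as sore throat, rhinorrhoea, headache and diarrhoea, easily attract another diagnosis.

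All four COVID-19 frequencies (confirmed, hospitalised, severe, lethal) rest on how cases are found. Section 9.1 gives descriptive data on confirmed cases as one reason for randomising 500 rather than 200, and the final report goes to regulators.

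There is also a question of comparability. The study doctor takes the call and, under section 8.4.2, also evaluates reactogenicity. Reactogenicity carries information about the arm, so an opinion-based filter need not act equally in both groups.

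**Working it through.** The protocol gives no expected case count, power or efficacy figure for COVID-19, so there is no planned figure to reproduce. The check is a comparison of texts followed by illustrative arithmetic.

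**1. Trigger against endpoint.**
- Swab (8.3): temperature above 37.5 °C, one more symptom, and no other reason for the illness.
- Endpoint (5.3.1): clinical manifestations and positive RNA.
- An illness that meets the symptom criteria but is attributed elsewhere gets no study swab, although with a positive test it would be an endpoint case.

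**2. Could the loss be seen later?**
- N-protein IgM and IgG are tested at screening and Day 28 only (Table 14, footnote 4).
- After Visit 5 only serious adverse events and their treatments are registered (Table 14, footnotes 18 and 19).
- The separate form in section 8.3 describes the COVID-19 case. No record is named for a febrile illness that was explained away, or for the reason given.
- RBD and S-protein titres are measured at Month 6, but in vaccinees they also reflect the vaccine.

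From Day 28 to Month 6, missed cases could therefore not be recovered evenly in both arms.

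**3. Information about the arm.** Inputs: injection-site pain in Phase II at this dose, 72/129 = 0.558 on vaccine and 11/126 = 0.087 on placebo (Table 13); allocation 3:1.
- P(vaccine | pain) = 0.75 × 0.558 / (0.75 × 0.558 + 0.25 × 0.087) = 0.95
- P(vaccine | no pain) = 0.75 × 0.442 / (0.75 × 0.442 + 0.25 × 0.913) = 0.59

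Without this information the probability is 0.75.

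**4. Effect on the comparison.** Let a_v and a_p be the shares of true cases explained away on vaccine and placebo. Both are assumed; the protocol gives neither. At zero true efficacy, apparent efficacy = 1 − (1 − a_v)/(1 − a_p).
- Equal shares: 0 %. The ratio is unbiased, but each frequency is too low by that share.
- 10 % on vaccine, 5 % on placebo: 1 − 0.90/0.95 = 5.3 %.
- 5 % on vaccine, 10 % on placebo: 1 − 0.95/0.90 = −5.6 %.

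**5. What handling this needs.** If pain is the only cue, and x and y are the shares explained away in volunteers with and without earlier pain, then a_v − a_p = (0.558 − 0.087)(x − y) = 0.471(x − y). For 10 % against 5 %, x − y = 0.05/0.471 = 0.106, so y = 0.05 − 0.087 × 0.106 = 0.04 and x = 0.15. A gap of 15 % against 4 % is modest.

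**6. Scale in cases.** Placebo has 500/4 = 125 volunteers. At an assumed attack rate of 2 % to 10 %, 2.5 to 12.5 placebo cases occur. Losing an assumed 20 % of them removes 0.5 to 2.5 cases.

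**The case against.** The strongest reply is that little hangs on this. Section 3.4 makes protective efficacy exploratory because of the limited sample size. Section 9.2 presents the four endpoints descriptively, with Kaplan-Meier estimates if applicable and no test. The registration-driving interim comparison is on seroconversion and does not use the swab. All of that stands and limits the weight of the point.

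A reader might infer more than the documents support, in four ways.

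- *That the clause creates false protection.* The trial is double-blind: "neither the study doctor nor study participants will be aware of the vaccine" given, and the products look identical. Bias needs a guess formed from early reactions, persistence of that guess through Month 6, and different attribution by guessed arm. The direction is not fixed.
- *That the distortion is large.* Losses of 20 % against 5 % would give 1 − 0.80/0.95 = 16 %, and 30 % against 10 % would give 1 − 0.70/0.90 = 22 %. With pain as the cue these require explaining away about 34 % against 2 %, and 49 % against 6 %, of true cases by pain status. Such gaps are implausible, and nothing in the protocol supports them.
- *That an unswabbed illness can never become a case.* The endpoint asks for a positive laboratory RNA test and does not restrict it to the study swab. A positive result from outside care is not barred, which matters most for hospitalised, severe and lethal cases.
- *That vaccine reactions are a main route of loss.* Reactogenicity is assessed over 7 days, and cases in the first 14 days do not count.

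Section 8.3 also does not name who judges other reasons. That it is the study doctor is an inference from the phone-contact rule. None of this removes the mismatch between trigger and endpoint.

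**Conclusion.** The point holds as a weakness in case finding. Followed as written, section 8.3 gives no study swab to symptomatic volunteers whose illness is attributed elsewhere, on an undefined judgement that the endpoint does not require. The COVID-19 frequencies may therefore be understated, and after Day 28 the protocol provides little means of detecting it.

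Distortion between arms is possible but not demonstrated. The 5 % illustration rests on assumed losses, on pain being used as a cue and on different handling by guessed arm; reversing the losses reverses the sign. The share of cases lost cannot be derived from the protocol. The primary analysis, its significance levels and its power are untouched. This is a cheap improvement worth making, not a threat to the trial's main conclusion.

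**What to change.** In section 8.3, remove the absence of other reasons as a condition for the swab, so that everyone who meets the symptom criteria has the two PCR tests already planned. Record any alternative diagnosis as data on the COVID-19 form. Apply this at least from Day 15, when cases start to count.

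Applying it from Day 0 has some further merit, because section 9.2 excludes cases confirmed in the first 14 days from the efficacy analysis sets, so early swabbing also decides who is analysed. It would, however, send febrile vaccine reactions for testing; fever was reported in 21/129 vaccinees at this dose in Phase II (Table 13).

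From Day 15 the cost is one sentence, one field on the form and a small number of extra home swabs, limited to illnesses that would otherwise have been attributed elsewhere. The temperature threshold is a separate matter and is left as it stands.

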| Biochemistry | Screening, Day 2, Day 28 | Total protein, alanine aminotransferase (ALT), aspartate aminotransferase (AST), alkaline phosphatase (ALP), lactate dehydrogenase (LDH), total bilirubin, creatinine, urea, fasting glucose, C-reactive protein |
| Coagulation test | Screening, Day 2, Day 28 | Activated partial thromboplastin time (aPTT), prothrombin time (PT), fibrinogen |
| Urinalysis | Screening, Day 2, Day 28 | Specific gravity, pH, protein, glucose, erythrocytes, leucocytes, casts |

- - - 1. Blood IgE test

Evaluation of the IgE level will be carried out to assess the allergenic effect of the investigational products. Blood sampling will be performed during the screening period and on Day 28.

The analysis will be carried out at the central laboratory using the EIA. The investigators will be provided with a separate laboratory manual containing detailed instructions on handling biological samples (collection, storage and transportation).

- - - 1. Adverse Events

An adverse event (AE) is defined as any untoward medical occurrence in a clinical study subject administered a pharmaceutical product and which does not necessarily have a causal relationship with this treatment.

An adverse event can therefore be any unfavourable and unintended sign, symptom (including an abnormal laboratory finding), or disease temporally associated with vaccination (not registered in a volunteer before the study or occurring during the study, or, if pre-existing, worsening during the study after vaccination with investigational products), whether or not causally related to the investigation product.

An adverse drug reaction means any adverse event, the causal relationship of which with vaccination with the investigational products is assessed at least as possible (possible, probable, definite), i.e. the relationship cannot be ruled out.

An unexpected adverse drug reaction is an adverse event, the nature or severity of which is not consistent with the applicable vaccine information provided in the Investigator’s Brochure.

A serious adverse event (SAE) is any adverse event that:

- results in death
- life-threatening
- requires inpatient hospitalisation or prolongation of existing hospitalisation except for planned hospitalisation (before this study), in-hospital treatment of the AE not considered as a SAE and not resulted in hospitalisation, or social admission
- results in persistent or significant disability/incapacity

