This population will include subjects completed the randomisation and allocated into one of the study groups. This population will be used to provide the disposition of study subjects.

Safety Analysis Set

This population will include all randomised volunteers received a dose of the vaccine. It will be used for safety analysis.

Full Analysis Set (FAS, for immunogenicity analysis)

This analysis set will include all eligible volunteers from the safety population with at least one immunogenicity assessment result (for interim analysis, it should be obtained until Visit 5 [inclusive]). This set will be the main population for immunogenicity analysis.

Cellular immune response parameters will be analysed in the FAS subgroup for the analysis of vaccine efficacy including subjects with at least one cellular immunity assessment result.

Per-protocol Set (PPS, for immunogenicity analysis)

The population will include all eligible volunteers from the FAS received a dose of the vaccine according to the randomisation and study scheme and provided data for immunogenicity assessment before and after vaccination in line with the study scheme (for interim analysis, they should be obtained until Visit 5 [inclusive]). Such volunteers should not administer prohibited medications, should not have other major protocol deviations potentially affecting immunogenicity assessment and should not have confirmed COVID-19 cases within 14 days after vaccination. This set will be a supportive population for immunogenicity analysis.

Full Analysis Set (FAS, for efficacy analysis)

The population will include all eligible volunteers from the Safety Analysis Set contacted at least once after Day 14 excluding subjects with confirmed COVID-19 cases within 14 days after vaccination. This set will be the main population for efficacy analysis.

Per-protocol Set (PPS, for efficacy analysis)

The population will include all eligible volunteers from the FAS received a dose of the vaccine according to the randomisation and study scheme. Such volunteers should not administer prohibited medications, should not have other major protocol deviations potentially affecting efficacy assessment and should not have confirmed COVID-19 cases within 14 days after vaccination. This set will be a supportive population for efficacy analysis.

- - 1. General Provisions

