Efficacy variable (antibody geometric mean titer (GMT) and neutralising antibody GMT) will be presented and compared by evaluation time points based on the calculated 95 % confidence interval using ANOVA/ANCOVA following the logarithmic transformation of base 10. The ANCOVA model will include the treatment group as a fixed factor, country/trial site as a factor and pre-existing (log-transformed) antibody titer as a covariate. Pre-existing anti-Ad5 neutralising antibody titers (low and negative (≤ 200) vs high (> 200)^1^), sex and age will be also considered as potential model factors. Mean log-transformed differences between the study groups (vaccine/placebo) will be evaluated with the corresponding 95 % confidence interval. The point estimates of the mean differences and the corresponding confidence intervals will be back-transformed.

Efficacy variable (geometric mean fold-rise in antibody titers and neutralising antibody titers) for each treatment group and each antibody GMT evaluation time point will be assessed with the corresponding two-sided 95 % CIs following log-transformation (log10), point estimation of the difference and confidence intervals, and back-transformation of obtained values. Between-group comparisons will be performed using ANOVA/ANCOVA following the logarithmic transformation of base 10. The ANCOVA model will include the treatment group as a fixed factor, country/trial site as a factor and pre-existing (log-transformed) antibody titer as a covariate. Pre-existing anti-Ad5 neutralising antibody titers (low and negative (≤ 200) vs high (> 200)^[[7]](#footnote-7)^), sex and age will be also considered as potential model factors.

Exploratory efficacy endpoints (frequency of confirmed COVID-19 cases during 6 months after vaccination, frequency of confirmed COVID-19 cases requiring hospitalisation, frequency of severe COVID-19 cases, and frequency of lethal COVID-19 cases (except for the cases occurred during the first 14 days after vaccination)) will be presented descriptively by treatment groups. Kaplan-Meier survival estimates will be also presented if applicable.

1. Safety Analysis

The safety analysis will be performed in the safety analysis set using descriptive methods.

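### Section 8.3 keeps confirmed COVID-19 out of adverse-event registration without saying how serious cases are reported, and cases in the first 14 days appear as an outcome in no planned by-arm output

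*Protocol*

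**What the plan says.** **Registration rule.** Section 8.3 closes with "Analysis of confirmed COVID-19 cases is the exploratory efficacy endpoint and they should not be registered as adverse events". Before that, it has the study doctor enter each case on a separate CRF form with onset and end dates, severity, need for hospitalisation and fatality. Case registration runs for 6 months, with no 14-day cut on capture.

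**SAE definition.** Section 8.4.2.8 begins "A serious adverse event (SAE) is any adverse event that" and lists the qualifying outcomes. Death is one; another is that the event "requires inpatient hospitalisation or prolongation of existing hospitalisation". The same section defines an adverse event broadly, as any untoward medical occurrence in a dosed subject. Its part on the investigator's SAE responsibilities asks for immediate reporting of all SAEs from vaccination to the end of the study, with the form sent within 24 hours.

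**COVID-19 endpoints.** Section 5.3.1 excludes the first 14 days from the overall case frequency and from each severity endpoint. For admissions the endpoint reads "Frequency of confirmed COVID-19 cases requiring hospitalisation (except for the cases occurred during the first 14 days after vaccination"). The next one, on severity, has the same cut: "Frequency of severe COVID-19 cases (except for the cases that occurred during the first 14 days after vaccination"). So does the one on deaths, which is given as "Frequency of lethal COVID-19 cases (except for the cases that occurred during the first 14 days after vaccination"). The efficacy analysis in section 9.2 repeats this: ("except for the cases occurred during the first 14 days after vaccination)) will be presented descriptively by treatment groups".

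**Analysis sets.** In section 9.2.1 the efficacy FAS is limited to eligible members of the safety set who were "contacted at least once after Day 14 excluding subjects with confirmed COVID-19 cases within 14 days after vaccination". The efficacy PPS is drawn from that FAS.

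**Safety analysis.** Section 9.2 tabulates AEs and SAEs by arm and names no COVID-19 output. The safety endpoints in section 5.3.2 are AEs to Day 28 and SAEs to Day 28 and to Month 6.

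**The concern.** There are two linked problems.

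First, a site whose volunteer is admitted to hospital with PCR-confirmed COVID-19 has no clear instruction. Under section 8.3 the case is not an adverse event, so by the definition in section 8.4.2.8 it cannot be a serious one. Under the broad adverse-event definition and the duty to report all SAEs, it is. About 10 sites in two countries may resolve this differently, and the SAE counts to Month 6 would then depend on local reading.

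Second, the rule that removes confirmed cases from safety rests on their being efficacy outcomes, but the efficacy definitions drop the first 14 days. The two exclusions overlap there. Severe or fatal COVID-19 soon after dosing is a safety question for any COVID-19 vaccine, and the protocol's own preclinical summary reports looking for antibody-dependent enhancement. The interim report, which supports a registration decision, would not show such cases by arm.

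**Working it through.** The protocol states no figure on this point, so the main check is to follow one case through the rules. Take a volunteer with a positive PCR on Day 10 who is hospitalised or dies.

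| Planned output | Rule | Does the case appear as an outcome? |
|---|---|---|
| Four COVID-19 endpoints | 5.3.1: first 14 days excluded | No |
| Efficacy FAS | 9.2.1: subjects with an early confirmed case removed; contact after Day 14 required | No; an early death fails both conditions |
| Efficacy PPS | 9.2.1: subset of that FAS | No |
| AE tables | 9.2: registered AEs; 8.3 bars registration of the case | No |
| SAE tables and 24-hour report | 8.4.2.8: an SAE is an AE; 8.3 says the case is not an AE | Not if 8.3 is followed literally; unclear in practice |
| COVID-19 CRF form | 8.3: dates, severity, hospitalisation, fatality | Recorded, but no stated analysis uses it |

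The FAS exclusion works on subjects. A case confirmed on Day 10 that becomes severe or fatal after Day 14 is therefore removed too.

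Now take a case confirmed on Day 60 and hospitalised. It does enter the descriptive efficacy tables. Only its status as an SAE is in doubt.

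**Size of the excluded window**

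- Full follow-up: 14/180 = 7.8% (14/182 = 7.7%).
- Interim analysis, data through Day 28: 14/28 = 50%.

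**Expected number of early cases.** The protocol gives no attack rate, so 6-month rates *A* of 1% to 10% are assumed, with a constant hazard over 182 days. The chance of a confirmed case in the first 14 days is p = 1 − (1 − A)^(14/182). The expected number is 500p for the full trial and 200p for the interim set. The chance of at least one among 500 is 1 − (1 − p)^500.

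| A (assumed) | Expected in 500 | Expected in first 200 (× 200/500) | Chance of at least one in 500 |
|---|---|---|---|
| 1% | 0.4 | 0.15 | 32% |
| 3% | 1.2 | 0.5 | 69% |
| 5% | 2.0 | 0.8 | 86% |
| 10% | 4.0 | 1.6 | 98% |

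These are confirmed cases of any severity; severe or fatal ones would be fewer.

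**The case against.** **Sections 8.3 and 8.4.2.8 can be read as consistent.** A specific rule removes an endpoint event from AE registration, and the SAE rule follows it. That reading is possible and is why the SAE consequence is an inference: nowhere does the protocol expressly exempt COVID-19 from SAE reporting. The inference still leaves sites without an instruction, since the general definition and the all-SAEs duty point the other way.

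**A reader might infer that every COVID-19 hospitalisation and death bypasses SAE reporting.** The documents do not support that.
- The bar covers confirmed cases only. An admission never confirmed by PCR remains an ordinary SAE.
- A temperature of 37.1 °C or higher is an AE under section 8.4.2, and so are cough, dyspnoea and the other listed general reactions in the first 7 days. Nothing withdraws them after confirmation.
- Section 8.4.2.8 lets the investigator and the QPPV report other safety matters that bear on risk and benefit. This route is discretionary, so it narrows the gap without closing it.

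**A reader might also infer that early cases enter no analysis at all.** That goes too far. The case is on the CRF, the subject stays in the Safety Analysis Set and may stay in the immunogenicity FAS, and a withdrawal or death would show in disposition. What is missing is the case itself as an outcome by arm.

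**An extra table is commonly left to the SAP.** This is fair for the table alone, because the data will exist. It does not answer the reporting rule, which sites follow from the protocol; a SAP cannot recover SAE reports that were never filed.

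**The early hazard is probably below average.** Entry requires negative PCR and serology and no recent contact or respiratory signs, and section 5.5 imposes strict precautions for exactly the first 14 days. This stands, and it makes 8% a likely upper bound.

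**Conclusion.** The point holds as a gap in reporting and tabulation. Section 8.3 does not say how PCR-confirmed cases that meet SAE criteria are reported, and its literal effect does not fit section 8.4.2.8; the passages must be reconciled. Separately, as written, an early confirmed case is an outcome in no planned by-arm efficacy or safety output, including the interim report.

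Under a constant hazard, early cases are at most roughly 8% of those over 6 months, probably fewer. The excluded window is half of the interim period. Under assumed 6-month attack rates of 1% to 10%, that means about 0.4 to 4 early cases of any severity among 500 volunteers, and about 0.15 to 1.6 among the first 200. With so few events the output would amount to a list of cases, but a single severe one would matter to a registration decision.

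The primary endpoint, its significance levels and its power are unaffected. The COVID-19 endpoints are exploratory and descriptive, and the 14-day exclusion is acceptable for them.

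**What to change.** 1. Amend the closing sentence of section 8.3, with a matching line in section 8.4.2.8, to state explicitly how confirmed COVID-19 cases meeting an SAE criterion are reported and how they count in the SAE endpoint to Day 28 and to Month 6.
2. Add to the safety analysis in section 9.2 one table or listing, in the Safety Analysis Set, of all confirmed cases by arm from Day 0. Split it at Day 14 and show severity, hospitalisation and death. Include it in the interim report.
3. Keep the 14-day exclusion for the exploratory efficacy endpoints.

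The cost is a short protocol amendment, some additional SAE reports if serious cases are routed that way, and one extra table. The section 8.3 form already collects the required fields, so no new data collection is needed.
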